**Methods and analysis:**

A prospective open cohort study between 1 January 2002 and 30 September 2014 will be based on the general population of people prescribed statins, using records from UK general practices contributing to the Clinical Practice Research Database (CPRD). Participants aged 25–84 years will enter the cohort on the date of their first prescription for a statin and leave on the earliest date of: a cardiovascular event; death; leaving the practice; the last practice upload date or the study end date. If there are no prescriptions within 90 days after the expected finishing date of a prescription, a patient will be defined as a stopper with the discontinuation outcome date as the expected finishing date. Rates of statin discontinuation will be calculated by calendar year, type and dose of statin, age, and morbidities. Cox proportional regression analyses will be run to identify the most important factors associated with discontinuation. Analyses will be run separately for patients without CVD (primary prevention) and with diagnosed CVD (secondary prevention).

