To explore the risks of statin discontinuation associated with the covariates, a Cox regression analysis will be undertaken. The model will include age, sex, ethnic group, deprivation quintile, calendar year at the entry to the cohort, baseline CVD risk and the type of statin prescribed at the baseline. Practices might differ in their prescription patterns, so we will account for clustering by practice. We shall calculate the adjusted HRs for baseline characteristics listed above: clinical values; chronic diseases; family history; use of other medications.

The proportional hazards assumption will be checked by using a log-log plot of survival for each variable. Variables which violate the assumption will be included into the model as a stratification factor. If clinically similar variables or categories (for smoking and ethnicity) are associated with similar risks, they will be combined. For continuous variables, recorded values will be used. For non-linear risk associations, fractional polynomials will be used if appropriate.^40^

As BMI, smoking status, systolic blood pressure and cholesterol/HDL ratio may be important patient characteristics but have non-negligible numbers of missing data, multiple imputation will be used to replace missing values.^41^ Five imputed data sets will be created, using multiple chained equations, and Rubin's rules will be used to combine effect estimates and SEs to allow for uncertainty due to imputing missing values. Calendar year; statin stopper status; log of survival time; age; years of records; potentially important characteristics; and type, dose and cumulative exposure to statins will be included in the imputation model.^42^

The main analyses will be run using the multiply imputed data. The least complete data are expected to be for cholesterol/HDL ratio, but information about this test is expected to be important for patient adherence. To ensure the robustness of our findings, we shall also run a sensitivity analysis including only patients with complete data.

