### Additional analyses

Patients might discontinue statins within the first year or after a longer period. The characteristics of these patients might differ, so we shall rerun the main analysis twice, in the first censoring all patients who did not discontinue before the end of year one, and in the second removing all patients who did discontinue before the end of year 1.

Some statin users have discontinuous use, with one or more restarts against a background of fairly continual usage. We shall define a subcohort in the study period for patients who discontinued statins (the outcome date in the main analysis will be their new entry date) and follow them until they have a new statin prescription or they are censored as described in the Study design section. We shall describe how many people restarted statin therapy within the first 6 months, 7–12 months and 12 or more months after their new entry dates using Kaplan-Meier estimates. We shall report descriptive statistics for the covariates listed above both for stoppers who restarted and those who did not.

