### Sensitivity analyses

Apart from the two sensitivity analyses already mentioned relating to exposure and missing values, two others will be included. One will be to facilitate comparison with the results of the Zhang *et al*^27^ study for long-term statin discontinuation. In this, we will define an outcome as an absence of any statin prescriptions within the 12 months (365 days) following the expected finishing date of a prescription. As before, the expected last date will also be the date of the outcome. Because of the longer period required for an outcome, for this analysis, we will remove patients with less than 2 years of follow-up records. The other will be run to investigate the influence of possible changes in baseline variables over the full study period, by rerunning the analysis with the follow-up period restricted to 5 years.

A 1% level of statistical significance will be used to allow for multiple comparisons. Stata V.13 will be used for all the analyses.

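### The imputation model holds one stopper status for all times, so the early and late reruns will understate any real difference between stopping in year 1 and after year 1 for the four imputed covariates

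*Protocol article*

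**What the plan says.** All places are in the protocol article.

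- **What is imputed (Statistical analysis).** Four covariates: "As BMI, smoking status, systolic blood pressure and cholesterol/HDL ratio may be important patient characteristics but have non-negligible numbers of missing data". The method is fixed: "Five imputed data sets will be created, using multiple chained equations, and Rubin's rules will be used".
- **What predicts the missing values (Statistical analysis).** "Calendar year; statin stopper status; log of survival time; age; years of records; potentially important characteristics; and type, dose and cumulative exposure to statins". This gives one stopper status and one time term. The status carries no gap length, but the stopper defined in the Abstract and the Outcome section is the 90-day one ("a patient will be defined as a stopper with the discontinuation outcome date as the expected finishing date"), so that is the natural reading.
- **Where the imputed data are used (Statistical analysis).** "The main analyses will be run using the multiply imputed data". A complete-case check is added: "we shall also run a sensitivity analysis including only patients with complete data".
- **Early and late reruns (Additional analyses).** The main analysis is run twice more, "in the first censoring all patients who did not discontinue before the end of year one", and then with those who stopped in year 1 removed. The stated reason is that the two kinds of stopper may have different characteristics.
- **365-day analysis (Sensitivity analyses).** "we will define an outcome as an absence of any statin prescriptions within the 12 months (365 days") after the supply should have ended, among patients with at least 2 years of follow-up records. The section does not say whether this analysis uses the same imputations, new ones or complete cases.

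**The concern.** An imputed covariate value is drawn from the relationship that the imputation model allows between that covariate and the outcome. With one status term, stoppers in month 3 and stoppers in year 6 receive the same shift in imputed BMI, smoking, blood pressure or cholesterol/HDL ratio, apart from what the log-time and cumulative-exposure terms absorb. The early and late reruns ask whether that shift differs, so the imputation model partly assumes away what they are meant to estimate.

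At stake is the comparison of predictors between early and late stopping. A covariate that matters only in year 1 would look somewhat weaker there and would show a small spurious association afterwards. The section expects cholesterol/HDL ratio to be both the least complete covariate and an important one for adherence, so the distortion would be largest where interest is high. With about 600 000 patients, sampling error will hide little of it.

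**Working it through.** **No plan figure to reproduce.** The article gives no missing fractions, stopping rates or period-specific effects. Everything numerical below rests on assumptions.

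**Why a single status is not enough.** Let x be the covariate, with log HR b1 in year 1 and b2 later. Let d1 and d2 indicate stopping in year 1 and after it, and let H1(T) and H2(T) be the cumulative baseline hazard accrued in each period up to time T. The density of x given the outcome is proportional to

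p(x) · exp{(b1·d1 + b2·d2)·x − H1(T)·e^(b1·x) − H2(T)·e^(b2·x)}.

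For small effects and standardised x, the mean shift is about b1·(d1 − H1) + b2·(d2 − H2). The two indicators need their own coefficients. A single status d = d1 + d2 forces them to be equal. If b2 = 0, late stoppers should resemble patients of the same follow-up who did not stop, but the single coefficient sets them apart. Log time recovers part of the early-late difference, not all of it.

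**Simulation 1.** 12 replicates of 8,000 patients; one normal covariate, missing completely at random; five imputations, averaged; Cox models for stopping before and after year 1. Baseline hazards are 0.30 per year in year 1 and 0.10 per year afterwards. The imputation model contains status and log time. HRs are per SD, and contrast = ln(early HR) − ln(late HR).

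| Assumed log HR, early / late | Missing | Full data, early / late | Imputed, early / late | Contrast, full | Contrast, imputed | Shrinkage |
|---|---|---|---|---|---|---|
| 0.3 / 0 | 20% | 1.343 / 1.004 | 1.325 / 1.017 | 0.2909 | 0.2646 | 9% |
| 0.3 / 0 | 50% | 1.342 / 1.010 | 1.305 / 1.051 | 0.2842 | 0.2165 | 24% |
| 0 / 0.3 | 20% | 1.006 / 1.348 | 1.024 / 1.321 | −0.2926 | −0.2547 | 13% |
| 0 / 0.3 | 50% | 0.997 / 1.340 | 1.053 / 1.280 | −0.2957 | −0.1952 | 34% |

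Example, second row: 1 − 0.2165/0.2842 = 0.238.

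**Adding log cumulative exposure** changes little here: for the 0.3 / 0 case the shrinkage is 8.5% at 20% missing (1.322 / 1.013) and 26% at 50% (1.295 / 1.049).

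**Same effect in both periods (log HR 0.2).** At 20% missing, early 1.218 against 1.221 and late 1.213 against 1.211. At 50%, early 1.214 against 1.213 and late 1.209 against 1.230, while the main HR also moved (1.211 against 1.222). The contrast moves by 0.004 and 0.018, which indicates the simulation noise. The 9% above is a move of 0.026, so it is approximate.

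**Simulation 2, true HRs 0.80 early and 1.00 late.** The true contrast is ln 0.80 = −0.2231.
- 20% missing: 0.811 and 0.989; contrast −0.2095 + 0.0111 = −0.1984; shrinkage 1 − 0.1984/0.2231 = 11%.
- 50% missing: 0.824 and 0.97; contrast −0.1936 + 0.0305 = −0.1631; shrinkage 27%.

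**After the change.** In simulation 2, separate early and late indicators restore the contrast. In simulation 1, a model with those indicators, further time terms and the 365-day outcome terms gives 1.341 / 1.003 at 20% and 1.351 / 1.013 at 50%, against full-data 1.343 / 1.004 and 1.342 / 1.010.

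**365-day outcome, if the same imputations were reused.** Assume that, per SD of the covariate, the log-odds that a 90-day stopper stays off treatment rise by 0.4. The full-data HR is 1.451 (20% run) and 1.450 (50% run). Status and log time give 1.389 and 1.304, a loss of 12% and 29% of the log HR. Adding cumulative exposure that counts later prescriptions gives 1.431 and 1.393, a loss of 4% and 11%.

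**The case against.** The strongest reply on the early and late runs is that they use the same 90-day event and time axis as the main analysis. Status and survival time, both in the imputation model, already place each event before or after year 1. This stands in part: it is why most of the contrast survives. A reader might infer that the imputed values cannot carry an early-late difference at all, and the simulations contradict that. What is missing is a separate coefficient for each period, and the reruns estimate exactly that.

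A reader might also infer that the 365-day analysis is fed by imputations built on the 90-day status. The article does not support this. It ties the imputed data to the main analyses, leaves the data source for the 365-day run open, and nowhere rules out re-imputation; a condensed article may leave that to the full plan. Cumulative exposure would also ease the problem if it runs to the last prescription, as the Statistical analysis section defines it. The Outcome section, however, bars later prescriptions from the discontinuation analysis, so whether it does is unclear. The 365-day run is meant for comparison with a published study, so less hangs on it.

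Finally, the complete-data analysis offers a partial check. It is promised for the findings in general and is not tied to the early and late reruns.

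**Conclusion.** The point holds in a limited form. With the listed variables, the early and late reruns understate a period difference for the four imputed covariates when there is one. The shrinkage of the log-HR contrast is roughly 10-25% for 20-50% missing when the effect is confined to year 1. It was somewhat more, 13% and 34%, in the simulated case of an effect only after year 1. These sizes depend on the assumed missing fractions, hazards and effects, and on effects that vanish entirely in one period.

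It does not follow that all rerun HRs are pulled toward the main result: with equal effects there is no material pull. The main HRs are not challenged. For the 365-day analysis the concern is conditional on reuse of the imputations, which is inferred and not stated. This is a cheap improvement to the imputation model, not a flaw in the primary results.

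**What to change.** In the Statistical analysis section, replace the single stopper status in the imputation variables with two indicators, stopping in year 1 and stopping after year 1, and keep log survival time and the other terms. State that the early and late reruns use these imputations.

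In the Sensitivity analyses section, state which data the 365-day analysis uses. If they are imputed, create a separate set with the 365-day stopper status and its survival time.

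The cost is a sentence or two and extra computing time. No new data are needed.

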### Additional analyses

Patients might discontinue statins within the first year or after a longer period. The characteristics of these patients might differ, so we shall rerun the main analysis twice, in the first censoring all patients who did not discontinue before the end of year one, and in the second removing all patients who did discontinue before the end of year 1.

Some statin users have discontinuous use, with one or more restarts against a background of fairly continual usage. We shall define a subcohort in the study period for patients who discontinued statins (the outcome date in the main analysis will be their new entry date) and follow them until they have a new statin prescription or they are censored as described in the Study design section. We shall describe how many people restarted statin therapy within the first 6 months, 7–12 months and 12 or more months after their new entry dates using Kaplan-Meier estimates. We shall report descriptive statistics for the covariates listed above both for stoppers who restarted and those who did not.

### Sensitivity analyses

Apart from the two sensitivity analyses already mentioned relating to exposure and missing values, two others will be included. One will be to facilitate comparison with the results of the Zhang *et al*^27^ study for long-term statin discontinuation. In this, we will define an outcome as an absence of any statin prescriptions within the 12 months (365 days) following the expected finishing date of a prescription. As before, the expected last date will also be the date of the outcome. Because of the longer period required for an outcome, for this analysis, we will remove patients with less than 2 years of follow-up records. The other will be run to investigate the influence of possible changes in baseline variables over the full study period, by rerunning the analysis with the follow-up period restricted to 5 years.

A 1% level of statistical significance will be used to allow for multiple comparisons. Stata V.13 will be used for all the analyses.

### Sample size calculation

All eligible patients will be used in the analyses, allowing investigation of different types of statins and facilitating identification of relevant patient characteristics associated with discontinuation. This approach is particularly important for the smaller group of patients already diagnosed with CVD at baseline.

About one million patients with at least one prescription of statin within the study period are available from the CPRD. Of these, just over one-third had a statin prescription in the past 12 months before the study entry or insufficient data for follow-up. Excluding these will leave about 600 000 patients available for analysis, one-quarter with CVD at the baseline.

For individual drug exposure, 5362 observations will be required to detect a HR of 0.9 or 1.1 at a significance level of 1% with 90% power between simvastatin and other statins. For common drugs such as atorvastatin and rarer drugs such as pravastatin (around 5% of exposure) we will have enough observations for all these drug types for both CVD and non-CVD groups. For rare drugs, such as rosuvastatin (less than 2% of exposure) and fluvastatin (less than 1% exposure), 1196 patients will be required to detect a clinically important HR of 0.8 at a significance level of 1% with 90% of power. We will have enough observations for both the CVD and non-CVD group for rosuvastatin, but only for the non-CVD group for fluvastatin.

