### Exposure

A number of statin users will have only one prescription before stopping. Because they did not receive a repeat prescription, it cannot be certain that these patients actually ever took statins. So, for the main analysis, having excluded patients with one prescription, we will run a sensitivity analysis including all patients with one or more prescriptions. We will report on the percentage of patients that had only one prescription and describe characteristics of this group.

The following statins will be included into the analysis: atorvastatin, simvastatin, fluvastatin, pravastatin and rosuvastatin. As the statin most commonly prescribed in the overall study period, simvastatin—used by around 70% of patients—will be used as the reference drug.

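### The required numbers 5362 and 1196 are total events for a 1:1 comparison, not patients, and 5362 does not cover HR 1.1, so the drug-by-drug adequacy statements do not follow from them

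*Protocol article*

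**What the plan says.** The section Sample size calculation gives two requirements. For individual drugs against simvastatin, "5362 observations will be required to detect a HR of 0.9 or 1.1 at a significance level of 1% with 90% power". For rare drugs, "1196 patients will be required to detect a clinically important HR of 0.8 at a significance level of 1% with 90% of power". It states no allocation ratio, no proportion expected to discontinue and no sidedness.

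From these figures it concludes that atorvastatin and pravastatin have enough observations in both prevention groups and that rosuvastatin does too. Numbers are said to suffice "but only for the non-CVD group for fluvastatin".

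The other inputs are also in the document:

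- Cohort size: "Excluding these will leave about 600 000 patients available for analysis, one-quarter with CVD at the baseline".
- The reference drug, simvastatin, is "used by around 70% of patients" (Exposure).
- Pravastatin is put at around 5% of exposure, rosuvastatin below 2% and fluvastatin below 1% (Sample size calculation).
- On the significance level: "A 1% level of statistical significance will be used to allow for multiple comparisons" (Sensitivity analyses).

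**The concern.** In a Cox or log-rank comparison, power depends on the number of events and on how patients divide between the two groups. A count of patients means something only once a proportion with the event is stated. Here the printed figures match event totals for two equal groups, while the protocol's own shares make the comparisons extremely unequal. One figure is also attached to two hazard ratios that are not equally far from 1 on the log scale.

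This paragraph is the only quantitative basis for the substantial power that the article lists among its strengths. Readers will use it to interpret null results for single drugs, above all fluvastatin in patients with CVD, where the protocol says in advance that numbers are too small.

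**Working it through.** **1. Reproducing the stated figures.** Schoenfeld's total number of events is D = (z₁₋α/₂ + z_power)² / [p(1−p)(ln HR)²]. With two-sided α = 0.01 and 90% power the numerator is 14.88. With p = 0.5:

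- HR 0.9: 5361.5, rounded up to **5362**, which matches.
- HR 0.8: 1195.3, rounded up to **1196**, which matches.
- HR 1.1: 6551.9, rounded up to **6552**, which does not match 5362.

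For HR 0.9 and HR 0.8, the one-sided version gives 4691 and 1046, and Freedman's formula gives 5372 and 1206. Of the variants tried, only two-sided Schoenfeld at 1:1 returns both printed figures. They are totals of events over both groups, and they equal patient numbers only if every patient stops.

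**2. HR 1.1.** Power is Φ(√(D·p(1−p))·|ln HR| − 2.576). With D = 5362 and p = 0.5: √1340.5 × 0.0953 = 3.490, and Φ(0.914) = 82%. The figure 5362 is right for HR 1/0.9 = 1.11.

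**3. The protocol's own shares.** Let p be the drug's share among users of that drug plus simvastatin (70%). The shares for rosuvastatin and fluvastatin are upper limits in the document.

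| Drug (share) | p | HR | Total events for 90% power | Of these on the drug |
|---|---|---|---|---|
| Pravastatin (5%) | 5/75 | 0.9 | 21 542 | 1436 |
| Pravastatin (5%) | 5/75 | 1.1 | 26 325 | 1755 |
| Rosuvastatin (2%) | 2/72 | 0.8 | 11 066 | 307 |
| Fluvastatin (1%) | 1/71 | 0.8 | 21 520 | 303 |

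**4. What the cohort would deliver.** The groups are 600 000 × 1/4 = 150 000 with CVD and 450 000 without. The section gives no stopping proportion, so a range is assumed: 10%, 26% and 50%. The Introduction cites 26% non-adherence in cardiovascular patients and more than 50% stopping at least temporarily. In the CVD group, the smaller of the two:

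| Comparison with simvastatin | Patients in the pair | Stopping needed for 90% power | Power at 10% / 26% / 50% stopping |
|---|---|---|---|
| Pravastatin 5%, HR 0.9 | 112 500 | 19.1% | 58.4% / 97.3% / >99% |
| Pravastatin 5%, HR 1.1 | 112 500 | 23.4% | 47.8% / 93.2% / 99.9% |
| Rosuvastatin 2%, HR 0.8 | 108 000 | 10.2% | 89.2% / >99% / >99% |
| Rosuvastatin or fluvastatin 1%, HR 0.8 | 106 500 | 20.2% | 55.5% / 96.4% / >99% |
| Fluvastatin 0.5%, HR 0.8 | 105 750 | 40.1% | 25.8% / 70.2% / 95.8% |

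Worked example (first row, 26%): 112 500 × 0.26 = 29 250 events; p(1−p) = 0.0622; √1820 × 0.1054 = 4.495; Φ(1.919) = 97%.

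In the non-CVD group at 26% stopping, power exceeds 99% for pravastatin, for rosuvastatin at 1% to 2%, and for fluvastatin at a share of 0.5% to 1%.

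**The case against.** The strongest reply is that nothing depends on these figures. All eligible patients are analysed, so no recruitment target, model or significance level changes. That stands, and it limits the weight of the point.

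A second reply is that the two main slips largely cancel if the figures were compared with users of each drug. The document does not state that comparison, though the pattern of its conclusions fits it. Against a very large reference group, pravastatin needs 1436 on-drug events for HR 0.9, which 5362 users supply if 1436/5362 = 27% stop. For HR 0.8, 303 to 307 on-drug events come from 1196 users if 25% to 26% stop. This stands as arithmetic, but the offset holds only near that stopping proportion, which the section never states.

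Third, HR 1.1 may be a rounding of 1.11, for which 5362 is exact. That is a plausible origin. As printed, the 90% claim for 1.1 is still wrong.

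Fourth, a condensed article may leave the allocation and the event proportion to a fuller document. That would excuse their absence. It does not excuse printed figures with the wrong unit, or one figure that does not fit its stated hazard ratio.

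A reader might also infer that the study is badly underpowered, because 5362 events split 5:70 would give only 26% power for HR 0.9 and 20% for HR 1.1. The documents do not support that reading. It supposes 5362 events in the whole comparison, whereas the CVD group alone would yield about 29 250 at 26% stopping.

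**Conclusion.** The paragraph is wrong as written, at minor to moderate importance. The figures 5362 and 1196 are event totals at 1:1 for HR 0.9 and HR 0.8, mislabelled as observations and patients. HR 1.1 needs 6552 events at 1:1, 22% more than stated. At the protocol's shares the total events needed are several times larger: about four times 5362 for pravastatin at HR 0.9 (21 542), and about nine times 1196 for rosuvastatin at a 2% share (11 066).

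It would go too far to say that the drug-by-drug conclusions are wrong. The positive ones probably hold because the cohort is so large, and they weaken only if stopping is much rarer than the Introduction suggests, at about 10%. The negative one, for fluvastatin in the CVD group, is undetermined. At 26% stopping, power is 96% at a 1% share and 70% at 0.5%, and the document says only that the share is below 1%. The statement may be too pessimistic, or it may be right.

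The power figures assume that the overall exposure shares describe patients by drug and apply equally in both prevention groups, that stopping is similar across drugs, and that nothing is lost to clustering by practice or covariate adjustment. The 26% is a borrowed non-adherence figure, not an estimate under this protocol's definition. The reproduction of 5362 and 1196 and the HR 1.1 result need none of these assumptions.

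**What to change.** Rewrite the last paragraph of the sample size section:

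1. Label the figures as total events and state two-sided α = 1%.
2. Give HR 0.9 and HR 1.1 separately, or state HR 1.11 in place of 1.1.
3. For each drug, use D = 14.88/[p(1−p)(ln HR)²], with p its share among users of that drug plus simvastatin, by prevention group if the shares differ.
4. Convert events to patients with a stated assumed proportion discontinuing in each prevention group, and show a range.
5. Restate each drug's adequacy from these results, including fluvastatin in the CVD group, using its actual share instead of an upper limit.

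The cost is one paragraph of text. No extra data are needed and the analysis does not change. Some required totals will look less favourable than those printed, while the statement on fluvastatin in CVD may become more favourable.
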